#### Subgroup analyses for the primary outcome

There will be three a priori defined subgroup analyses for the primary endpoint: (1) effectiveness of the FFVM vs. RFVM in ICUs according to the PRE-DELIRIC score (patients with a predicted risk < 25%, 25–50%, 50–75%, and > 75%); (2) effectiveness of the FFVM vs. RFVM according to patient group (medical vs. surgical and neurocritical vs. non-neurocritical); and (3) effectiveness of the FFVM vs. RFVM in ICUs according to APACHE-II scores (≤15 vs. > 15 points). The consistency of intervention effects across the above-mentioned subgroups will be assessed by means of tests for interaction. The Bonferroni correction will be applied to adjust the subgroup analyses for multiple comparisons.

#### Secondary outcomes

We will use the following statistical procedures to evaluate the study secondary outcomes:*Daily hazard of delirium*: The daily hazard of delirium will be analyzed using a joint survival model that accounts for the treatment effect (with adjustment for the cluster effect, period effect, and interaction between cluster and period) on repeated daily indicator of delirium within each patient and terminating event (death or discharge from the ICU) [22]. This outcome will be presented as hazard ratio (HR) and 95% CI.*Any ICU-acquired infections*: The differences in the cumulative incidence of any ICU-acquired infection between the FFVM and RFVM groups will be compared using generalized estimating equations with adjustment for the cluster effect, period effect, and interaction between intervention and period. This outcome will be presented as RR and 95% CI.*Ventilator-free days*: The number of ventilator-free days will be evaluated using the 7-day time horizon. Ventilator-free days will be set to 0 for patients who have died. The differences in the mean ventilator-free days between the FFVM and RFVM groups will be compared using generalized estimating equations with adjustment for the cluster effect, period effect, and interaction between intervention and period. This outcome will be presented as mean difference (MD) and 95% CI.*ICU length of stay*: The differences in the mean ICU length of stay between the FFVM and RFVM groups will be compared using generalized estimating equations with adjustment for the cluster effect, period effect, and interaction between intervention and period. This outcome will be presented as MD and 95% CI.*Hospital mortality*: The differences in hospital mortality rates between the FFVM and RFVM groups will be compared using generalized estimating equations with adjustment for the cluster effect, period effect, and interaction between intervention and period. This outcome will be presented as RR and 95% CI.*Symptoms of anxiety and depression among family members*: The differences in the mean HADS scores for anxiety and depression between the FFVM and RFVM groups will be compared using generalized estimating equations with adjustment for the cluster effect, period effect, and interaction between intervention and period. These outcomes will be presented as MD and 95% CI.*Satisfaction among family members*: The differences in the mean CCFNI satisfaction scores between the FFVM and RFVM groups will be compared using generalized estimating equations with adjustment for the cluster effect, period effect, and interaction between intervention and period. This outcome will be presented as MD and 95% CI.*Prevalence of burnout among the ICU professionals*: Burnout is defined as a cumulative MBI score greater than − 9. The differences in the prevalence of burnout between the FFVM and RFVM groups will be compared using generalized estimating equations with adjustment for the cluster effect and baseline MBI total scores. This outcome will be presented as prevalence ratio and 95% CI.

Given that the main safety outcomes of the present study are any ICU-acquired infections and burnout, we will not adjust these outcomes for multiple comparisons. For other secondary outcomes, the Bonferroni correction will be applied to adjust the analyses for multiple comparisons when appropriate, taking into consideration the number of comparisons within each population of interest (patients, family members, and ICU professionals).

We will perform sensitivity analyses to check the consistency of intervention effects on family members and ICU professionals as follows:Evaluation of study intervention effects on HADS subscale scores among family members, considering HADS scores as categorical variables with established cutoff points (> 10 points for both anxiety and depression subscales)Evaluation of study intervention effects on HADS subscale scores among family members adjusted by previous history of anxiety (for anxiety HADS subscale) and depression (for depression HADS subscale)Evaluation of study intervention effects on CCFNI subscale domains (information, proximity, reassurance, support, and comfort)Evaluation of study intervention effects on incidence (excluding individuals with burnout at baseline) and prevalence of burnout among ICU professionals, considering the following alternative MBI criteria:*Alternative criteria 1*: An emotional exhaustion subscale score ≥ 27, OR a depersonalization subscale score ≥ 10, OR a personal accomplishment subscale score ≤ 33*Alternative criteria 2*: An emotional exhaustion subscale score ≥ 27, OR a depersonalization subscale score ≥ 10*Alternative criteria 3*: An emotional exhaustion subscale score ≥ 27, AND a depersonalization subscale score ≥ 10, AND a personal accomplishment subscale score ≤ 33.

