## Statistical analysis plan

### Overall principles

The main analysis for each outcome will be performed at the subject level using the intention-to-treat (ITT) principle, meaning that all participants with a recorded outcome will be included in the analysis and will be analyzed according to the treatment group to which they were randomized (FFVM or RFVM), independent of actual visiting hours. Moreover, all analyses will account for the cluster-randomized crossover design to ensure correct type I error rates and confidence intervals (CIs). A significance level of 0.05, adjusted for multiple comparisons when appropriate, will be used for all statistical comparisons. Analysis will start once all data to discharge for the last included patient have been obtained, the database has been cleaned and locked, and the SAP has been submitted for publication. The R Development Core Team software will be used for analysis [18].

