Self-perception of involvement in patient care					
Score:^e^ mean (SD)	xx.x (xx.x)	xx.x (xx.x)	MD	x.xx (x.xx-x.xx)*	x.xx
ICU professionals					
Satisfaction of ICU professionals with the ICU visiting policy score:^f^ mean (SD)	xx.x (xx.x)	xx.x (xx.x)	MD	x.xx (x.xx-x.xx)*	x.xx

*BSI* bloodstream infection, *CCFNI* Critical Care Family Needs Inventory, *CI* confidence interval, *FFVM* flexible family visitation model, *HADS* Hospital Anxiety and Depression Scale, *HR* hazard ratio, *ICU* intensive care unit, *MD* mean difference, *PR* prevalence ratio, *RFVM* restrictive family visitation model, *RR* risk ratio, *SD* standard deviation, *UTI* urinary tract infection

^a^Adjusted for multiple comparisons with Bonferroni correction when appropriate

^b^According to the Confusion Assessment Method for the Intensive Care Unit (CAM-ICU) criteria

^c^According to the Centers for Disease Control and Prevention (CDC) criteria

^d^Maslach Burnout Inventory (MBI) total score > − 9

^e^The self-perception of involvement in patient care score varies from 0 (no involvement) to 27 (maximum degree of involvement)

^f^The satisfaction of ICU professionals with the ICU visiting policy score varies from 0 (unsatisfied) to 4 (very satisfied)

^*^95% confidence interval

^**^99% confidence interval

^***^98.3% confidence interval

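### Seven secondary outcomes carry a 95% CI in the text but a 99% or 98.3% CI in Table 3, and the Bonferroni divisor behind the table is not stated

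*SAP article*

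**What the plan says.** The SAP article sets CI levels for the secondary outcomes in two places.

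- **Text under Secondary outcomes.** Each outcome has its own sentence, always with 95%. Daily hazard of delirium: "This outcome will be presented as hazard ratio (HR) and 95% CI". Ventilator-free days: "This outcome will be presented as mean difference (MD) and 95% CI". ICU length of stay and CCFNI satisfaction: "This outcome will be presented as MD and 95% CI". Hospital mortality: "This outcome will be presented as RR and 95% CI". The two HADS scores share a sentence that also gives 95%.
- **Table 3 (under Primary outcome).** Daily hazard, ventilator-free days, ICU length of stay and hospital mortality carry the two-star mark, defined as "99% confidence interval". HADS anxiety, HADS depression and CCFNI carry the three-star mark, defined as "98.3% confidence interval". ICU-acquired infection and burnout are at 95%, as in the text.

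Three statements govern multiplicity.

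- Overall principles: "A significance level of 0.05, adjusted for multiple comparisons when appropriate, will be used for all statistical comparisons".
- The paragraph that follows the list of secondary outcomes exempts two of them: "the main safety outcomes of the present study are any ICU-acquired infections and burnout, we will not adjust these outcomes for multiple comparisons". It applies Bonferroni to the others where appropriate, by the number of comparisons in each population (patients, family members, professionals).
- Footnote a of Table 3 says that the p values are Bonferroni-adjusted where appropriate.

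No divisor is given anywhere.

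**The concern.** Seven of the nine secondary rows in Table 3, hospital mortality among them, have two prespecified confidence levels. Nothing in the text marks the 95% as a level before adjustment. An analyst who follows the text and one who follows the table would print different intervals from the same data. The text's interval could also disagree with the adjusted p value in the same row. The purpose of the article is to settle such choices before the data are seen.

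Two smaller gaps go with this. The 99% level implies a divisor that does not obviously match the number of adjusted patient outcomes. And one section adjusts the significance level while a table footnote adjusts the p value, with no statement that only one of these applies.

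**Working it through.** **Inputs.** Overall alpha is 0.05 (Overall principles). Sidedness is not stated, so a CI of level 1 − alpha is taken as two-sided. Patient secondary outcomes: 5 listed, 4 once infection is exempted. Family secondary outcomes: 3. Table 3 levels: 99% and 98.3%.

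**Step 1: count the conflicts.**

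| Outcome | Text | Table 3 |
|---|---|---|
| Daily hazard of delirium | 95% | 99% |
| Ventilator-free days | 95% | 99% |
| ICU length of stay | 95% | 99% |
| Hospital mortality | 95% | 99% |
| HADS anxiety | 95% | 98.3% |
| HADS depression | 95% | 98.3% |
| CCFNI satisfaction | 95% | 98.3% |
| ICU-acquired infection | 95% | 95% |
| Burnout | 95% | 95% |

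4 + 3 = 7 conflicts. The two exempt outcomes agree, so the star marks look deliberate.

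**Step 2: reproduce the Table 3 levels.** Bonferroni level = 1 − 0.05/k.

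- k = 3: 1 − 0.0167 = 98.33%, printed as 98.3%. This matches the three family outcomes.
- k = 5: 1 − 0.01 = 99.00%. This matches the patient rows.
- k = 4: 1 − 0.0125 = 98.75%. This does not match. Rounding does not explain it, because the table prints one decimal elsewhere and 98.75% would appear as 98.8%.

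So the table reproduces with k = 5 for patients and k = 3 for family members.

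**Step 3: CI beside p value.** Assume that the interval and the raw p value come from the same test. With raw p = 0.03, the 95% CI excludes the null. The adjusted p is 0.03 × 5 = 0.15 for a patient outcome (0.03 × 4 = 0.12 if k = 4) and 0.03 × 3 = 0.09 for a family outcome. None is below 0.05. The 99% and 98.3% CIs include the null and agree with the adjusted p value.

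**Step 4: interval width.** Normal quantiles are 1.960 (95%), 2.394 (k = 3), 2.498 (98.75%) and 2.576 (99%).

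- 99% against 95%: 2.576/1.960 = 1.314, so 31% wider.
- 98.3% against 95%: 2.394/1.960 = 1.221, so 22% wider.
- 99% against 98.75%: 2.576/2.498 = 1.031, so about 3% wider.

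For the hazard ratio and risk ratio these are widths on the log scale.

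**Step 5: familywise error if significance is read from the CI alone (independence).**

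| Outcomes | Level | Chance of at least one false exclusion of the null |
|---|---|---|
| 4 patient | 95% | 1 − 0.95^4 = 18.5% |
| 3 family | 95% | 1 − 0.95^3 = 14.3% |
| 4 patient | 99% | 1 − 0.99^4 = 3.9% |
| 4 patient | 98.75% | 1 − 0.9875^4 = 4.9% |

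Without independence, the sum of the alphas bounds the error: 0.20, 0.15, 0.04 and 0.05.

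**Step 6: where the divisor and double adjustment matter.** The choice between k = 5 and k = 4 changes a decision only for raw p between 0.01 and 0.0125. For example, p = 0.011 becomes 0.055 with k = 5 and 0.044 with k = 4. If an adjusted p value were also compared with an adjusted threshold, the raw p would have to fall below 0.01/5 = 0.002 for a patient outcome.

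**The case against.** The strongest reply is that the intention can be recovered. Overall principles, the multiplicity paragraph and footnote a of Table 3 all say that these outcomes are adjusted, and Table 3 gives adjusted CI levels. The 95% phrase is a stock ending, used for the tertiary outcomes too, and the multiplicity paragraph follows directly. The likely explanation is text that was not updated. This stands: it shows which of the two places to change. It does not remove the conflict, because the text still states a presentation level outcome by outcome.

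A reader might infer that the significance rule is undetermined, or that Bonferroni control is lost. The document does not support that. The p values in Table 3 are adjusted, and a test decision taken from them is controlled. The 18.5% and 14.3% arise only if the adjusted p values are ignored and significance is read from 95% CIs, which the SAP nowhere instructs.

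A reader might also infer that 99% is an arithmetic error and that 98.75% is the only correct level. That is not shown either. The divisor of 5 is back-calculated. The SAP refers to the number of comparisons within each population, which can be read as all five patient secondary outcomes, or as the four adjusted ones plus the primary. A divisor of 5 is valid and conservative, with total alpha 4 × 0.01 = 0.04 over the four outcomes.

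**Conclusion.** The conflict is literal and should be corrected: seven secondary outcomes have 95% in the text and 99% or 98.3% in Table 3. Used as written, the text gives intervals too narrow to match the adjusted p values. The table's intervals are 31% wider than the text's for the patient outcomes and 22% wider for the family outcomes, on a normal approximation. The familywise figures depend on independence and on reading significance from the 95% CIs.

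The divisor is a lesser point. It is unstated, and 5 sits awkwardly with four adjusted patient outcomes, but it costs only about 3% in CI width and inflates no error.

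This is a consistency error confined to secondary outcomes. The primary outcome, infection and burnout are at 95% in both places and are unaffected.

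**What to change.** 1. In the text under Secondary outcomes, replace 95% with the Table 3 level for the seven outcomes. Keep 95% for ICU-acquired infection and burnout.
2. State the divisor for each population. For family members it is 3. For patients, either keep 5 and 99% and say that this is a deliberate conservative choice, or use 4 and 98.75% and change the two-star footnote of Table 3 to match.
3. State that either the p value is adjusted and compared with 0.05, or the raw p value is compared with a reduced threshold, but not both.

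The cost is wording in the SAP and the table shell; no data collection or sample size is touched. When the article was written, recruitment was still open and analysis was to wait for database lock, so the choice could be recorded before any results were known.

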#### Baseline characteristics

The baseline characteristics of all participants will be presented by study arm in a table (see Table 2), but no formal statistical hypothesis testing will be performed to avoid unnecessary testing.

**Table 2 Tab2:** Baseline characteristics of study participants

	FFVM	RFVM
Patients		
Age, years: mean (SD)	xx.x (xx.x)	xx.x (xx.x)
Age ≥ 65 years: *n*/total *n* (%)	x/x (xx.x)	x/x (xx.x)
Female gender: *n*/total *n* (%)	x/x (xx.x)	x/x (xx.x)
Charlson comorbidity index: median (IQR)	xx.x (xx.x-xx.x)	xx.x (xx.x-xx.x)
History of dementia: *n*/total *n* (%)	x/x (xx.x)	x/x (xx.x)
Hazardous alcohol consumption:^a^ *n*/total *n* (%)	x/x (xx.x)	x/x (xx.x)
ICU admission type		
Medical: *n*/total *n* (%)	x/x (xx.x)	x/x (xx.x)
Emergency surgery: *n*/total *n* (%)	x/x (xx.x)	x/x (xx.x)
Elective surgery: *n*/total *n* (%)	x/x (xx.x)	x/x (xx.x)
PRE-DELIRIC score: mean (SD)	xx.x (xx.x)	xx.x (xx.x)
APACHE-II score:^b^ mean (SD)	xx.x (xx.x)	xx.x (xx.x)
SOFA score:^b^ mean (SD)	xx.x (xx.x)	xx.x (xx.x)
Mechanically ventilated: *n*/total *n* (%)	x/x (xx.x)	x/x (xx.x)
Use of vasopressor: *n*/total *n* (%)	x/x (xx.x)	x/x (xx.x)
Use of corticosteroids: *n*/total *n* (%)	x/x (xx.x)	x/x (xx.x)
Use of parenteral sedative:^b^ *n*/total *n* (%)	x/x (xx.x)	x/x (xx.x)
Use of benzodiazepine:^b^ *n*/total *n* (%)	x/x (xx.x)	x/x (xx.x)
Use of opioid:^b^ *n*/total *n* (%)	x/x (xx.x)	x/x (xx.x)
Indwelling central venous catheter: *n*/total *n* (%)	x/x (xx.x)	x/x (xx.x)
Urinary catheter: *n*/total *n* (%)	x/x (xx.x)	x/x (xx.x)
Family members		
Age, years: mean (SD)	xx.x (xx.x)	xx.x (xx.x)
Female gender: *n*/total *n* (%)	x/x (xx.x)	x/x (xx.x)
Years of education: mean (SD)	xx.x (xx.x)	xx.x (xx.x)
Household income, USD: median (IQR)	xx.x (xx.x-xx.x)	xx.x (xx.x-xx.x)
Unemployed: *n*/total *n* (%)	x/x (xx.x)	x/x (xx.x)
Living with care recipient: *n*/total *n* (%)	x/x (xx.x)	x/x (xx.x)
Surrogate decision maker: *n*/total *n* (%)	x/x (xx.x)	x/x(xx.x)
History of anxiety: *n*/total *n* (%)	x/x (xx.x)	x/x (xx.x)
History of depression: *n*/total *n* (%)	x/x (xx.x)	x/x (xx.x)
ICU professionals		
Age, years: mean (SD)	xx.x (xx.x)	xx.x (xx.x)
Female gender: *n*/total *n* (%)	x/x (xx.x)	x/x (xx.x)
Type of ICU professional		
Physician: *n*/total *n* (%)	x/x (xx.x)	x/x (xx.x)
Nurse: *n*/total *n* (%)	x/x (xx.x)	x/x (xx.x)
Nurse technician: *n*/total *n* (%)	x/x (xx.x)	x/x (xx.x)
Physiotherapist: *n*/total *n* (%)	x/x (xx.x)	x/x (xx.x)

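### The ventilator-free-days model leaves out baseline mechanical ventilation, a collected and strongly prognostic covariate, and so gives up precision

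*SAP article*

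**What the plan says.** The Secondary outcomes section fixes the model term by term: "mean ventilator-free days between the FFVM and RFVM groups will be compared using generalized estimating equations with adjustment for the cluster effect, period effect". An intervention-by-period interaction completes the model. The count runs over 7 days, and "Ventilator-free days will be set to 0 for patients who have died".

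Table 2 (Baseline characteristics) has a patient row "Mechanically ventilated". Unlike APACHE-II, SOFA and the sedative, benzodiazepine and opioid rows, it carries no footnote extending it over the first 24 hours after inclusion, so it reads as status at entry. The table is descriptive only: "no formal statistical hypothesis testing will be performed to avoid unnecessary testing".

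No other analysis brings this variable into the ventilator-free-days comparison:

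- The PRE-DELIRIC adjustment and the other analyses under Sensitivity analyses for the primary outcome concern delirium, as do the subgroup analyses.
- The sensitivity analyses listed at the end of Secondary outcomes cover family members and ICU professionals only.

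Elsewhere the SAP does use baseline information in a main secondary model: burnout is compared "with adjustment for the cluster effect and baseline MBI total scores".

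**The concern.** Over a 7-day horizon, entry status largely sets where a patient can finish. A survivor who was not ventilated at entry and stays off the ventilator scores near 7; a patient ventilated at entry starts losing days at once. Leaving that variable out puts its share of the variance into the residual. Table 3 gives this outcome a 99% interval, so the standard error matters more here than for an outcome judged at 5%.

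A second, weaker consideration is robustness. Patients are recruited after the ICU's visiting model is in force (Trial overview; Fig. 1). Two Table 1 exclusions leave room for local judgement: predicted stay under 48 hours, and no family member available for flexible visits. If these were applied differently under the two models, the ventilated share could differ systematically, and an unadjusted comparison would carry that difference.

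**Working it through.** The SAP states no effect size, standard deviation, power or ventilated share for this outcome, so there is no figure to reproduce.

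**Inputs from the SAP.** 40 ICUs with 25 patients per phase, so 40 × 25 = 1000 patients per model at full recruitment. Level 1%, from the 99% interval in Table 3. (The Secondary outcomes text says 95% for the same outcome; R² and the relative cut in standard error do not depend on this.) Two-sided testing is assumed.

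**Assumed inputs.** Ventilated share p = 10-50%. Gap in mean ventilator-free days g = 1.5-4.5. Standard deviation 2.5 in patients ventilated at entry and 1.5-2.2 in the others. No design effect.

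**Step 1, variance explained.** R² = p(1−p)g² / [p(1−p)g² + W], with W = p·SD₁² + (1−p)·SD₀². The standard error is multiplied by √(1−R²).

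| p | g | SD₀ | p(1−p)g² | W | R² | Cut in SE |
|---|---|---|---|---|---|---|
| 0.10 | 1.5 | 2.2 | 0.20 | 4.98 | 0.04 | 2% |
| 0.30 | 3.0 | 2.2 | 1.89 | 5.26 | 0.26 | 14% |
| 0.30 | 3.0 | 1.5 | 1.89 | 3.45 | 0.35 | 20% |
| 0.30 | 4.5 | 1.5 | 4.25 | 3.45 | 0.55 | 33% |

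The first and last rows are the extremes of the grid. In patient numbers, 1/(1−R²) runs from 1.04 to 2.2.

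**Step 2, interval width at p = 0.30, g = 3.** SE = √(2 × variance/1000). With SD₀ = 1.5 it goes from √(2 × 5.34/1000) = 0.103 to √(2 × 3.45/1000) = 0.083. The 99% half-width (× 2.576) goes from 0.27 to 0.21 days. With SD₀ = 2.2 it goes from 0.31 to 0.26 days.

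**Step 3, power.** For an effect with 80% unadjusted power at the 1% level, adjusted power = Φ[(2.576 + 0.842)/√(1−R²) − 2.576].

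- R² = 0.05: Φ(0.93) = 82%
- R² = 0.20: Φ(1.25) = 89%
- R² = 0.35: Φ(1.66) = 95%

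**Step 4, chance imbalance.** At p = 0.30 the standard deviation of the difference in ventilated share is √(2 × 0.3 × 0.7/1000) = 2.0 percentage points. Times 3 days, that moves the estimate by about 0.06 day, against an unadjusted standard error of 0.10-0.12.

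**Step 5, simulation of the design.** 3000 runs of 40 ICUs × 2 periods × 25 patients were generated with no visiting effect, about 30% ventilated and a gap of about 3 days before truncation to 0-7. They were analysed by cluster-period means rather than GEE, at the 5% level.

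- Chance imbalance only: the unadjusted estimate averaged 0.002 and rejected 5.2% of the time. Its empirical standard deviation was 0.093, against 0.075 adjusted, and (0.093/0.075)² = 1.54, or roughly half as many patients again.
- Systematic gap in ventilated share imposed: 3 points moved the unadjusted mean by −0.08 day and 5 points by −0.13 day. The adjusted mean stayed within 0.003 of zero. Across all scenarios the adjusted analysis rejected 4.7-5.5% of the time. Selection here acts only through ventilation status, so adjustment removes it by construction.

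**The case against.** The strongest reply is that nothing is broken. A GEE that respects the clustering and crossover is a valid analysis without patient-level covariates, this is one of several secondary outcomes, and the SAP makes no promise that it breaks. All of that stands.

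It can also be said that the gain cannot be fixed from the document. That stands too: at the low end, 80% power becomes only about 82%. But no value in the range makes adjustment harmful, and the covariate costs almost nothing.

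Three stronger readings are tempting, and the document does not support them:

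- **A reader might infer that any imbalance in ventilated patients would pass as a visiting effect.** Chance imbalance is already within the unadjusted interval (steps 4 and 5). Each ICU serves both models, so stable differences in case mix between ICUs largely cancel. Only a systematic difference would bias the result. The SAP describes consecutive patients and one set of criteria for both models; it leaves room for such a difference but does not show one. If selection did occur, a single yes/no covariate might not remove all of it.
- **A reader might infer that the burnout model shows the SAP contradicting itself.** There the same instrument is measured at baseline and as outcome. Ventilation at entry is a binary status, while the outcome is a count that also reflects later intubation and death. The comparison shows that baseline adjustment is accepted in this plan, not that there is an inconsistency.
- **A reader might extend the point to hospital mortality and APACHE-II.** Table 2 marks that score as covering the first 24 hours after inclusion, so it can contain data from after entry. The mean-value rule under Handling of missing data is set for PRE-DELIRIC components. No gain has been quantified for mortality.

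**Conclusion.** The point holds as a missed gain in precision on one secondary outcome, with some added robustness. It does not show an invalid analysis or demonstrated bias. The omission is a stated choice: the model terms are listed, and the SAP says its statistical procedures do not differ from the protocol.

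The conclusion that precision is lost needs only that ventilation at entry predicts ventilator-free days, which follows from how the outcome is counted. The size rests on the assumed share, gap and standard deviations, and on ignoring the design effect. At a mid-range 30% share and 3-day gap, the standard error would fall by about 14-20%. Protection against systematic imbalance is a reason in favour, but no false-positive rate can be attached to this trial, because nothing in the document fixes the size of such an imbalance.

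**What to change.** In the ventilator-free-days paragraph of Secondary outcomes, add mechanical ventilation at inclusion (yes/no) as a prespecified patient-level covariate in the GEE. State that status is taken at inclusion. Report the adjusted mean difference as the main estimate in Table 3 and keep the current unadjusted mean difference as supportive.

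The cost is one sentence of SAP text and one model term. The variable is already collected, and the SAP places itself before the end of recruitment and database lock. For a mean difference on the identity scale, adjustment does not change the quantity being estimated. Any missing ventilation status can go through the site queries already planned under Handling of missing data. Fixing the choice now also avoids a post hoc decision if Table 2 later shows unequal shares. No change to the hospital-mortality model is proposed.

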Years of experience in ICU: mean (SD)	xx.x (xx.x)	xx.x (xx.x)
Hours of work per week: mean (SD)	xx.x (xx.x)	xx.x (xx.x)
Number of patients per professional		
Physician: mean (SD)	xx.x (xx.x)	xx.x (xx.x)
Nurse: mean (SD)	xx.x (xx.x)	xx.x (xx.x)
Nurse technician: mean (SD)	xx.x (xx.x)	xx.x (xx.x)
Physiotherapist: mean (SD)	xx.x (xx.x)	xx.x (xx.x)
Burnout syndrome at baseline:^c^ *n*/total *n* (%)	x/x (xx.x)	x/x (xx.x)

*APACHE-II* Acute Physiology and Chronic Health Evaluation-II, *FFVM* flexible family visitation model, *ICU* intensive care unit, *IQR* interquartile range (P25–P75), *PRE-DELIRIC* PREdiction of DELIRium in ICU patients, *RFVM* restrictive family visitation model, *SD* standard deviation, *SOFA* Sequential Organ Failure Assessment, *USD* United States dollars

^a^Alcohol consumption greater than or equal to 14 units per week for women and greater than or equal to 21 units per week for men

^b^Within the first 24 h of inclusion in the study

^c^Maslach Burnout Inventory total score > − 9

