#### Sensitivity analyses for the primary outcome

We aim to conduct the following sensitivity analyses for the primary outcome to assess consistency and the risk of bias:Evaluation of study intervention effects adjusted by the baseline risk of delirium according to the PRE-DELIRIC score.Evaluation of study intervention effects considering the cluster adherence to FFVM implementation. In this analysis, the study intervention effects will be adjusted by the total fidelity of FFVM implementation score.Evaluation of study intervention effects considering the potential confounding effect of sedation on the delirium diagnosis. In this analysis, the study intervention effects will be evaluated, considering patients with positive CAM-ICU during ICU stay in the context of Richmond Agitation-Sedation Scale (RASS) score – 2 or − 3 as non-delirious subjects.Evaluation of effects of study interventions, considering a best plausible scenario/worst plausible scenario imputation of outcomes among ICUs that did not complete the patient recruitment as follows:*Best plausible scenario*: Imputation of the lowest study cluster/phase incidence of delirium for missing FFVM patients and the highest study cluster/phase incidence of delirium for missing RFVM patients*Worst plausible scenario*: Imputation of the lowest study cluster/phase incidence of delirium for missing RFVM patients and the highest study cluster/phase incidence of delirium for missing FFVM patients.

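### No risk-adjusted analysis of hospital mortality or ICU-acquired infection is planned, although baseline predictors of both are collected

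*SAP article*

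**What the plan says.** The plan for mortality stands under Secondary outcomes: "The differences in hospital mortality rates between the FFVM and RFVM groups will be compared using generalized estimating equations". The only model terms named are cluster, period and intervention-by-period, and the result is a risk ratio with a 95% interval. Infection is handled in the same way: "The differences in the cumulative incidence of any ICU-acquired infection between the FFVM and RFVM groups will be compared" by a GEE with the same three terms.

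Table 2 (Baseline characteristics) lists, by arm, age, Charlson index, admission type, APACHE-II, SOFA, mechanical ventilation, central venous catheter and urinary catheter. Its footnote b gives the time window for APACHE-II and SOFA: "Within the first 24 h of inclusion in the study". The section rules out baseline testing and sets no rule for acting on an imbalance.

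Baseline-risk adjustment is planned for other outcomes:
- Delirium, as a sensitivity analysis: "Evaluation of study intervention effects adjusted by the baseline risk of delirium according to the PRE-DELIRIC score".
- HADS anxiety and depression, as sensitivity analyses adjusted for a history of the same condition.
- Burnout, whose main model includes the baseline MBI total score.

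The APACHE-II subgroup analysis is limited to the primary outcome. The sensitivity analyses listed for secondary outcomes concern only family members and ICU professionals.

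**The concern.** Mortality is the gravest outcome in the trial, and infection is one of the two outcomes that the plan names as main safety outcomes. By the plan's own practice elsewhere, both would be expected to have a supportive risk-adjusted analysis.

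In a cluster design this matters more than in an individually randomised trial. The ICU, not the patient, is randomised. According to the Fig. 1 legend, each phase opens with 15 days in which the model runs and local investigators adapt the staff to it before anyone is recruited, so they know the model when they enrol. Several exclusions in Table 1 need judgement: the expected length of stay, the chance of surviving the first day, and whether a relative is free to take part in flexible visits. The last refers directly to the intervention. If such judgements differed between the two phases of an ICU, the resulting difference in case mix could be read as an effect of the visiting model. An adjustment chosen after Table 2 is seen would be data-driven, which the Discussion says this publication is meant to avoid.

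**Working it through.** **What the models contain.** Every mention of mortality, infection, APACHE-II, SOFA, PRE-DELIRIC and adjustment in the SAP article was compared.

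| Outcome | Baseline-risk covariate | Where |
|---|---|---|
| Delirium | PRE-DELIRIC | Sensitivity analyses for the primary outcome |
| HADS | History of anxiety or depression | Secondary outcomes, sensitivity analyses |
| Burnout | Baseline MBI score | Secondary outcomes, main model |
| Hospital mortality | None | – |
| Any ICU-acquired infection | None | – |

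There is no plan figure to reproduce: the article states no mortality rate, infection rate or power for these outcomes. What follows illustrates size under assumptions.

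**Inputs from the document.** 40 ICUs × 2 phases × 25 patients = 2,000, about 1,000 per model.

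**Assumed inputs.** Hospital mortality p of 15-35%; APACHE-II SD 7; log-odds of death b of 0.05-0.11 per point; design effect DE 1.0-1.5.

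**Risk ratio from a case-mix shift alone.** Average risk is the mean of expit(a + b·score) over a normal score, with a chosen so that the mean equals p. The scores are then shifted by d points and the new mean is divided by p.

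| Shift d | Risk ratio over the grid |
|---|---|
| 0.5 point | 1.02-1.04 |
| 1 point | 1.03-1.09 |
| 2 points | 1.06-1.19 |

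**Against the sampling error.** SE(log RR) = √[DE × 2(1−p)/(1000p)].
- p = 0.35, DE = 1.0: √(2 × 0.65/350) = 0.061.
- p = 0.15, DE = 1.5: √(1.5 × 2 × 0.85/150) = 0.130.

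For a spurious risk ratio of 1.06, log 1.06 = 0.058, which is 0.45 to 0.96 standard errors. Two-sided rejection at the 5% level then rises to about 7-16%. At the 1% level, which matches the 99% interval marked for mortality in Table 3, it rises to about 2-5%.

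**Would the shift be visible?** The chance SE of the difference in mean APACHE-II is 7 × √(2/1000) = 0.31, or 7 × √(3/1000) = 0.38 with DE 1.5. A 1-point difference is therefore about 2.6 to 3.2 standard errors and would stand out in Table 2.

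**Precision.** In simulations of 2 × 1,000 patients (mortality 18-30%, b = 0.08-0.12, SD 7.5, robust Poisson, clustering ignored), the adjusted-to-unadjusted variance ratio for log RR was 0.85-0.95, a cut of 5-15%. In standard-error terms this is 1 − √0.95 = 3% to 1 − √0.85 = 8%. With a weaker slope the gain is smaller.

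**Infection.** If ventilated patients have three times the risk and 35% rather than 30% are ventilated at baseline, the risk ratio is (1 + 2 × 0.35)/(1 + 2 × 0.30) = 1.70/1.60 = 1.06. Both the threefold risk and the split are assumptions. The split is itself 0.05/√(2 × 0.325 × 0.675/1000) = 2.4 standard errors, ignoring clustering.

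**The case against.** An intention-to-treat comparison without patient covariates is a valid main analysis of a secondary outcome. That stands, and nothing in the mortality or infection model is wrong or contradictory.

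A reader might go further and infer that enrolment is selective, that a severity difference between models is to be expected, and that the planned mortality risk ratio will be biased. The document does not support this. The Trial overview specifies consecutive patients, and Table 1 applies one set of exclusions in both phases. Each ICU also serves both models, so stable differences between ICUs cancel; only selection that differs between the phases of the same ICU would remain. A typical chance imbalance of 0.3-0.4 APACHE-II point moves the risk ratio only to about 1.01-1.03, and the standard error already allows for chance.

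Three further points stand:
- APACHE-II and SOFA are taken in the 24 hours after inclusion, when the visiting model is already in force, so they are not strictly pre-exposure covariates.
- The mean-value rule under Handling of missing data is written for the components of PRE-DELIRIC, not for a mortality model.
- The section on adherence mentions sensitivity and exploratory analyses of outcomes by FFVM implementation. It would therefore be too strong to say that mortality has no sensitivity analysis of any kind. Those analyses concern fidelity, not baseline risk.

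These points limit the claim and shape the remedy. They do not explain why delirium, HADS and burnout are risk-adjusted while mortality and infection are not.

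**Conclusion.** The gap is real but modest. No baseline-risk-adjusted analysis of hospital mortality or ICU-acquired infection is planned, although the variables are collected and the plan adjusts other outcomes. Differential selection between phases could occur and could be read as an effect; the SAP does not show that it does.

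All sizes rest on assumed mortality, slope and SD. The 1-point illustration (risk ratio 1.03-1.09) is small against a standard error of 0.06-0.13 on the log scale. The bias would become substantial only with a shift of about 2 points. The gain in precision is likewise useful rather than large. The case for acting is that pre-specified adjustment costs almost nothing and settles in advance how an imbalance in Table 2 will be handled.

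**What to change.** Keep the current GEEs as the main analyses. Before database lock, pre-specify one supportive covariate-adjusted GEE for each outcome:
- **Hospital mortality:** add age, Charlson index, admission type and one continuous severity score (APACHE-II or SOFA, chosen now). State that the score is taken within 24 hours after inclusion, and also show the result without it.
- **Any ICU-acquired infection:** add baseline mechanical ventilation, central venous catheter and urinary catheter.
- **Missing covariates:** state a simple fill rule for these models, since the existing mean-value rule covers only PRE-DELIRIC components.

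The cost is a few sentences in the SAP, a little more analysis and no new data. The section declaring no differences from the protocol would need a line if the protocol lacks these analyses. The article reports 1,591 patients enrolled with recruitment still open, and analysis starts only after lock, so the addition could still be made in advance. The drawbacks are a single-value fill for a few missing scores and a severity score measured shortly after exposure begins; showing the model without the score deals with the second.
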